# Prevention of post-concussion-like symptoms in patients presenting at the emergency room, early single eye movement desensitization, and reprocessing intervention versus usual care: study protocol for a two-center randomized controlled trial

**DOI:** 10.1186/s13063-018-2902-2

**Published:** 2018-10-12

**Keywords:** Stress, Emergency department, Eye movement desensitization and reprocessing, Post-concussion-like symptoms, Post-traumatic stress disorder, Clinical trial

## Abstract

**Background:**

Recent data suggest that 10–20% of injury patients will suffer for several months after the event from diverse symptoms, generally referred to as post-concussion-like symptoms (PCLS), which will lead to a decline in quality of life. A preliminary randomized control trial suggested that this condition may be induced by the stress experienced during the event or emergency room (ER) stay and can be prevented in up to 75% of patients with a single, early, short eye movement desensitization and reprocessing (EMDR) psychotherapeutic session delivered in the ER.

The protocol of the SOFTER 3 study was designed to compare the impact on 3-month PCLS of early EMDR intervention and usual care in patients presenting at the ER. Secondary outcomes included 3-month post-traumatic stress disorder, 12-month PCLS, self-reported stress at the ER, self-assessed recovery expectation at discharge and 3 months, and self-reported chronic pain at discharge and 3 months.

**Methods:**

This is a two-group, open-label, multicenter, comparative, randomized controlled trial with 3- and 12-month phone follow-up for reports of persisting symptoms (PCLS and post-traumatic stress disorder). Those eligible for inclusion were adults (≥18 years old) presenting at the ER departments of the University Hospital of Bordeaux and University Hospital of Lyon, assessed as being at high risk of PCLS using a three-item scoring rule. The intervention groups were a (1) EMDR Recent Traumatic Episode Protocol intervention performed by a trained psychologist during ER stay or (2) usual care. The number of patients to be enrolled in each group was 223 to evidence a 15% decrease in PCLS prevalence in the EMDR group.

**Discussion:**

In 2012, the year of the last national survey in France, 10.6 million people attended the ER, some of whom did so several times since 18 million visits were recorded in the same year. The SOFTER 3 study therefore addresses a major public health challenge.

**Trial registration:**

Clinical Trials. NCT03400813. Registered 17 January 2018 – retrospectively registered.

**Electronic supplementary material:**

The online version of this article (10.1186/s13063-018-2902-2) contains supplementary material, which is available to authorized users.

## Background

In 2012, when the latest national survey was conducted in France, 10.6 million people reported having attended the emergency room (ER), some of whom did so several times since 18 million ER visits were recorded in the same year [1]. In general, over 90% of those attending the ER will be discharged within hours, without hospitalization [2].

Recent consistent observations [3–6] that 10–20% of injury patients will suffer for several months after the event from diverse symptoms, with a subsequent decline in quality of life that can be significant and delay or prevent the resumption of school or work activities, as well as changing social and family relationships, are of major public health consequences. Approximately 2 million people each year in France are confronted by difficulties of varying degrees whose cause is often unidentified and unrelated to the traumatic event. This link is all the more difficult to make as these symptoms appear to be non-specific, and include headaches, concentration disorders, memory problems, stress intolerance, personality change, and irritability. These symptoms have been described for more than 50 years in the context of head trauma, and were therefore referred to as post-concussion syndrome (PCS). Surprisingly, the most recent results show that these symptoms are not specific to brain injuries and can occur in other patients presenting to the ER [5, 7, 8], greatly expanding the size of the population concerned. In a cross-sectional, observational study of 31,958 high school athletes, Iverson et al. [9] also found that 19% of uninjured boys and 28% of uninjured girls reported having a symptom burden resembling an ICD-10 diagnosis of PCS; thereafter, these symptoms were frequently described as post-concussion-like symptoms (PCLS).

Recognizing that brain damage is not the main cause of these symptoms, researchers have compared patients with and without PCLS with two objectives, namely to predict their occurrence and to understand why they occur. This framework led to the major conclusion that psychological vulnerability, on the one hand, and stress experienced during and in the aftermath of the event, on the other, are the two best predictors of these lasting symptoms. This finding has been repeatedly observed in studies that assess the factors associated with PCLS [9–15].

The study of post-traumatic stress disorder (PTSD) has received renewed interest in view of the psychological pain of soldiers from Western countries returning from overseas following medical trauma, shedding light on this major public health phenomenon also affecting patients who have suffered an accident, physical assault, or an acute medical condition and whose general health remains precarious several months or years later. These studies have led to a better characterization of PTSD, including the individualization of four dimensional components, namely re-experiencing, avoidance, hyperactivation of the nervous system, and cognitive and emotional numbing [16]. Symptoms of PCLS are very similar and even sometimes exactly the same as the last two dimensions of PTSD (hyperactivation of the nervous system and cognitive and emotional numbing). This led various authors to hypothesize that PCLS and PTSD partly share the same causal pathway, in which stress plays a key role. This would be particularly relevant for prevention of PCLS, in particular because, in contrast to PTSD studies, PCLS studies include insufficient numbers and are of low quality to identify credible modes of intervention [17].

Our research team has conducted two studies in the past 10 years that enabled us to further our understanding of PCLS and to look for prevention opportunities. In 2007, we conducted a cohort study of 2018 patients with mild traumatic brain injuries and 1447 other injury patients recruited in the adult ER of Bordeaux University Hospital (Pericles project) [8, 10]. Follow-up to 12 months provided an unprecedented database allowing for in-depth comparisons of patient subgroups. It was this study that showed that PCS, despite its name, was not specific to head trauma [8], and highlighted the importance of stress and the overlap between PCS and PTSD [8, 10]. The data obtained allows us today to compare the performance of risk assessment tools designed to select patients at increased risk of PCS from variables measured in the ER. This last point is of major importance in the preparation of this protocol.

Following the Pericles project, we conducted a pilot study to identify the factors explaining the persistence of symptoms 3 months after an injury event. The key result of this pilot study (manuscript submitted) was that the stress level reported by patients at the end of their ER stay was a powerful predictor of PCLS and PTSD, irrespective of the stress level reported on entering the ER. This important result prompted us to consider testing the feasibility and then the effectiveness of stress management interventions during an ER stay, in the hope of improving the outcomes of traumatized patients.

Results from the literature and these two studies led us to initiate a literature search for the best intervention candidates that would have the potential to lower stress levels during an ER stay.

One of the first ideas proposed for patients who experience a stressful event was to initiate a stress management procedure before the consolidation of stressful memories. This is partly why the practice of psychological debriefing, which consists of debriefing sessions conducted 2–10 days after the critical incident, has been widely disseminated. However, several critical reviews [18] and a Cochrane review [19] have concluded that this form of intervention leads to an increased rate of PTSD.

More promisingly, early exposure therapy, which is based on the extinction of fear through engagement with traumatic memories and clues, appears to be an effective treatment of PTSD [20, 21]. PTSD syndrome can be interpreted as a failure of recovery caused, in part, by failure of the extinction of trauma [22]. This is supported by research conducted on animals showing that early extinction has the potential to alter the consolidation of memory of original fear [23–25]. Rothbaum et al. [18] were the first to show the effectiveness of an extinction-type intervention (prolonged exposure) beginning in the ER in the prevention of PTSD in a sample of 137 patients randomized to three groups. The intervention also included two other sessions 1 and 2 weeks later. The same authors showed that such short-term intervention could also lower PTSD risk in patients with genes previously found to be associated with stress response [26]. Trauma-focused cognitive behavioral therapy delivered within weeks of a potentially traumatic event for people showing signs of distress was also effective in the treatment of acute stress and early PTSD symptoms, and in the prevention of PTSD [27–31].

However, the psychotherapeutic intervention that has thus far proven superior to all other methods is eye movement desensitization and reprocessing (EMDR). Conceived by Francine Shapiro [32], EMDR is an empirically validated psychotherapeutic approach that can rapidly process disturbing experiences adaptively together with the aid of eye movements or other forms of bi-lateral stimulation. Several meta-analyses and Cochrane reviews have shown that this is one of the most effective treatments for PTSD [32–35]. Treatment may be started soon after the trauma, but most often after a complaint from the patient who is already suffering from PTSD symptoms. More recently, a study by Tarquinio et al. [36] showed the effectiveness of an EMDR-based intervention initiated in the first 48 h. The target population of this study was workers who have suffered professional violence (assaults, robberies, etc.).

A study conducted in Israel showed very promising results with a single-session, early modified EMDR session provided in a general hospital inpatient and outpatient setting to 86 patients with acute stress syndrome suffering from intrusion distress following accidents and terrorist bombing attacks [37]. Half of the patients reported immediate fading of intrusive symptoms and general alleviation of distress, 27% described partial alleviation of their symptoms and distress, while 23% reported no improvement. At the 4- and 6-month follow-up, the immediate responders in the terror victims group remained symptom free, while the non-responders endorsed more risk factors for PTSD. These results support other anecdotal reports on the rapid effects of brief EMDR intervention on intrusive symptoms in early uncomplicated post-traumatic cases.

Following the recognition of the failure of psychological debriefing, the issue of difficult access to patients with high levels of stress or dissociation was raised. This was all the more critical as it was known that dissociation at the time at which exposure therapy starts was associated with a poorer response [18]. In response to this challenge and to the increasing number of patients in need of care after manmade catastrophes such as bomb attacks, modified EMDR procedures and protocols adapted for early intervention have been developed to help victims and can be applied soon after trauma, including the emergency response procedure (ERP) [38] and the recent traumatic episode protocol (R-TEP) [39, 40].

The ERP is a short procedure implemented according to procedures designed and tested in emergency contexts, including the ER [40, 41]. The individuals who arrive at the ER show a wide range of disturbance. The greatest benefit of the ERP intervention is expected for patients in a ‘highly agitated’ state (scoring 7–10/10 on the Subjective Units of Disturbance scale, where 0 = no disturbance and 10 = the highest disturbance possible) to those who have moved into a ‘silent terror’ (scoring 10+/10 on the Subjective Units of Disturbance scale).

The R-TEP is an early EMDR current trauma-focused intervention that incorporates and extends the main ideas of the original Recent Event Protocol guidelines first described by Shapiro and Laub in 2008 [42].

The ICD-10 established a set of diagnostic criteria for PCS. In order to meet these criteria, a patient must have had a head injury *“usually sufficiently severe to result in loss of consciousness*” followed by the development, within 4 weeks, of at least three of the eight following symptoms: headache, dizziness, fatigue, irritability, sleep problems, concentration problems, memory problems, and problems tolerating stress. There is relatively little systematic research on the prevention and treatment of PCS [43–46]. A systematic review published in 2010 [45] suggested that cognitive behavioral therapy may be effective in the treatment of PCS. However, the authors found no quality studies and call for more rigorous trials of cognitive behavioral therapy for post-concussion symptoms. Other strategies include information, education and reassurance [47–49]. An emerging literature points to the independent impact of expectations and coping on chronic conditions following trauma, in particular for patients with whiplash and low back pain [50–55]. Reassurance, as provided in the context of cancer [50], low back pain [51, 52], and mild head trauma [47, 49], was found to help patients in their recovery process. It is therefore possible that at least a subgroup of patients who experienced a traumatic injury may benefit from such intervention.

Available research data, both from our studies and that available in the literature, led us to select the EMDR R-TEP procedure. This choice was based on the following considerations:The absence of sufficient literature related to preventive interventions for PCLSThe partial overlap between PCLS and PTSDThe results of our preliminary studies strongly suggesting that stress plays a major role in PCLSThe consensus for the use of EMDR in early prevention of PTSDThe growing evidence of a significant psychological component to persistent complaintsThe failure of early psychological debriefing to prevent PTSD

We then conducted a new pilot study [53], intended to examine the feasibility of stress management sessions during the ER stay with candidate interventions as selected by our literature search. To this end, we conducted a randomized open-label, single-center study to assess the feasibility of psychologist-led interventions in the context of the ER and to compare the effect of EMDR with reassurance and usual care. Conducted in the ER of Bordeaux University Hospital, the study included patients with a high risk of PCLS randomized into three groups, as follows: (1) a 15-min reassurance session, (2) a 60-min session of EMDR, and (3) usual care. Main outcomes were the proportion of interventions that could be carried out and the prevalence of PCLS and PTSD 3 months after the ER visit.

A total of 130 patients with a high risk of PCLS were randomized. No logistic problem or patient refusal was observed. In the EMDR, reassurance and control groups, the proportions of patients with PCLS at 3 months were 18%, 37%, and 65% and those with PTSD were 3%, 16%, and 19%, respectively. The relative risk for PCLS adjusted for the type of event (injury, non-injury) for the comparison between EMDR and control was 0.24 (95% CI 0.095–0.61). This first randomized controlled trial therefore shows that a short EMDR intervention is feasible and potentially effective in the context of the ER. The study was registered at ClinicalTrials.gov (NCT03194386).

The present protocol aims to replicate the latter trial in order to confirm or reject our hypothesis of a beneficial impact of early R-TEP EMDR on PCLS and PTSD in two different ERs. SPIRIT Checklist for this trial is provided as an Additional file 1.

### Potential benefit

The trial is designed to test the impact of early EMDR intervention on PCLS and PTSD in patients presenting to the ER. In 2012, the year of the last national survey in France, 10.6 million people attended the ER, some of whom several times, since 18 million visits were recorded that year. The SOFTER 3 study therefore addresses a major public health challenge.

## Methods/design

The main objective in our two-site, open-label, randomized controlled trial is to compare the impact on 3-month PCLS of early EMDR R-TEP intervention and usual care in patients presenting to the ER. Secondary objectives include the comparison between EMDR R-TEP and control of 3-month PTSD, 12-month PCLS, self-reported stress at ER discharge, self-assessed recovery expectation at discharge and 3 months, and self-reported pain at discharge and 3 months.

The outcomes are therefore defined as follows:

Primary outcome3-month PCLS as measured with the Rivermead Post-Concussion Symptoms Questionnaire [54]Secondary outcomes12-month PCLS as measured with the Rivermead Post-Concussion Symptoms Questionnaire3-month PTSD as measured with PTSD Checklist-5 [55]Self-assessed recovery expectation at discharge and 3 monthsSelf-reported chronic pain at 3 monthsSelf-reported acute pain at dischargePsychotropic medicine use at 3 months as measured by drug delivery data extracted from the Caisse national d’assurance maladie des travailleurs salariés (CNAM-TS) database, the French social insurance system

### Randomization and blinding

Patients will be allocated to one of the two arms with block randomization by clinical center sites. Statistical analysis will be performed blinded to arm content, revealed only by the Data Safety Monitoring Board (DSMB) report. It is not possible to blind the participants to their allocation due to the nature of the intervention.

### Inclusion criteria

All patients attending the adult ER of one of the study sites following an event that led to an injury, or with a new acute medical condition, will be assessed for inclusion. The inclusion criteria are as follows:Age 18 and aboveConscious, able to provide informed consent, able to understand study procedures and to comply with them for the entire length of the study; French speakerInjured, whatever the cause of injury (the event causing the injury must have occurred in the past 12 h) or experiencing a medical event associated with an acute medical condition and presenting for the first time to the ER for this reasonScore resulting from the screening tool > 1: female: + 1, taking at least one anxiolytic treatment: + 1, perceived health status prior to admission: excellent, very good 0; good: + 1; poor: + 2; bad + 3Affiliated to the French insurance system

### Exclusion criteria

Any candidates to whom any of the exclusion criteria apply at baseline will be excluded from study participation. The exclusion criteria are as follows:Acute drug or alcohol use or dependence that, in the opinion of the site investigator, would interfere with adherence to study requirementsInability or unwillingness of individual or legal guardian/representative to give written informed consentInability or unwillingness to be contacted for 3- and 12-month follow-up interviews

### Study enrollment procedures and randomization

Study protocol and time of collection of outcomes are presented in Figs. 1 and 2. Participants will be recruited among patients presenting to the ERs of the University Hospital of Bordeaux (Groupe Hospitalier Pellegrin) and Lyon (Groupement Hospitalier Edouard Herriot) and assessed with a high risk of PCLS. The identification and recruitment of potential study participants will be carried out by emergency personnel under the supervision of the project manager as soon as the patient’s condition permits and in all cases after the initial clinical evaluation conducted in the framework of the usual care. First oral consent will then be sought for participation in the assessment stage, which consists in selecting patients with a high risk of PCLS.

**Fig. 1 Fig1:**
[figure not shown]
Overview study diagram

**Fig. 2 Fig2:**
[figure not shown]
Schedule of enrolment, interventions, and assessments

A set of three items will be recorded for each injured patient, including sex (+ 1 for female), perceived health status prior to admission (excellent, very good: 0; good: + 1 poor: + 2; bad: + 3), current use of anxiolytics/antidepressants (+ 1 if yes).

To be enrolled in the study, the patient will need to score above a pre-defined threshold of 2 on the scoring procedure based on the three items and designed to select patients at risk for PCLS. The score has been developed using data from the Pericles study and validated on data of the SOFTER Pilot 1 and 2 studies.

Patients fulfilling inclusion criteria and assessed as at risk for PCLS will be presented with the objective and procedures and invited to sign an informed consent form. A screening log will be filled in to describe reasons for ineligibility and for non-participation of eligible candidates.

The randomization procedure for assigning a participant to an intervention group will then be performed and the results will be recorded in the Shared Study Monitoring System. Electronic block randomization will be stratified according to study center. Block sizes will be randomly modified and kept secret.

### Intervention

Patients in the EMDR group will receive a 1-hour psychotherapeutic intervention, utilizing the R-TEP [40]. This protocol is specially designed for victims of recent traumatic events, and incorporates and extends the early EMDR intervention protocols [32] into an integrative and comprehensive intervention considering the fragmented, unconsolidated nature of recent traumatic memories and the need for safety and containment. Following the eight phases of the standard EMDR protocol, it introduces four new procedural concepts (Traumatic Episode, Episode Narrative, “Google Search/ Scan” for identifying disturbing fragments and Current Trauma Focused processing strategies). These sessions will be carried out by trained psychologists.

Patients in the treatment-as-usual group will be medically and psychologically attended to by ER staff with no intervention of the study psychologist.

### Sample size

The study sample size is calculated using PCLS rates expected at 3 months after an ER admission in a patient population assessed to be at high risk of PCLS.

Our pilot study showed that, using the criteria described above, the incidence of PCLS among patients selected and enrolled in the study will be of approximately 47%. Our aim is to design the present study to be able to evidence a 15% decrease in PCLS prevalence in the EMDR group. Assuming an alpha risk of 5% and a power of 80%, the required sample size will be 169 patients in each group. We further assumed 20% loss to follow-up and 5% missing data for the main variables. Thus, we plan to include 223 patients in each group (112 per center in each group).

A study therapist will be available from 10 am to 6 pm, 5 days a week. Considering EMDR session duration and emergency care, patients will be assessed for eligibility from 8 am to 6 pm. Data from our ER registry and experience from our pilot study show that, during this period, approximately 50 patients will be assessed for eligibility. The screening tool used in this study will select approximately 10% of patients admitted to the ER. We also estimate that 10% of eligible patients will be missed in the ER and assume a 5% refusal rate. Consequently, we can expect approximately four inclusions per day, corresponding to an inclusion period of 3 months.

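### The stated 80% power at 169 per group is not the power of the named primary test: Fisher's exact test gives 78.0% there and needs 180 per group

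*Protocol article*

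**What the plan says.** The Sample size section gives a base rate, an effect and a result:

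- Base rate, attributed to a pilot study that is not named: "the incidence of PCLS among patients selected and enrolled in the study will be of approximately 47" per cent.
- Effect: "Our aim is to design the present study to be able to evidence a 15% decrease in PCLS prevalence in the EMDR group".
- Result: "Assuming an alpha risk of 5% and a power of 80%, the required sample size will be 169 patients in each group".
- After allowing for 20% loss to follow-up and 5% missing data: "we plan to include 223 patients in each group".

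It gives neither the formula nor whether the 5% is one- or two-sided.

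The Data analyses section makes Fisher's exact test the primary analysis. It also mentions a stratified analysis by centre and PCLS risk score, but not as the primary test. Randomization is in blocks stratified by centre (Study enrollment procedures and randomization).

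For the randomized pilot in high-risk patients, the Background reports: "In the EMDR, reassurance and control groups, the proportions of patients with PCLS at 3 months were 18%, 37%, and 65" per cent.

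**The concern.** Fisher's exact test is conservative with two groups of this size, so a sample size from the usual normal-approximation formula gives it less power than the formula promises. The plan states 80% and names Fisher's test without linking the two. Readers of a null result will take 80% as the chance the trial had of detecting the planned effect, so the figure should belong to the test that produces the p-value.

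Two wording matters affect how that figure is read. A 15% decrease can mean percentage points or a relative reduction, and the Abstract gives no base rate from which to tell. The 47% is the planning rate, yet the only usual-care rate that the article reports for high-risk patients is 65%.

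**Working it through.** **Inputs.** Usual-care rate 0.47, effect 15%, 80% power, 5% level, 169 evaluable per group, 20% loss and 5% missing data (Sample size); Fisher's exact test (Data analyses). Assumptions: two-sided 5% (a one-sided level gives 131, which does not fit 169), and the effect read as 0.47 to 0.32.

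**1. Reproduce the plan's figure.** The pooled-variance formula for two proportions, with mean rate p̄ = 0.395, is

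n = [1.960·√(2p̄(1−p̄)) + 0.8416·√(p₁(1−p₁) + p₂(1−p₂))]² / (p₁−p₂)²

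- First term: 1.960·√0.47795 = 1.3550.
- Second term: 0.8416·√(0.2491 + 0.2176) = 0.5750.
- n = (1.9300)² / 0.0225 = 165.5, so 166 per group.

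The stated 169 is close to this and slightly above it. Normal-approximation power at 169 is Φ[(0.15·√169 − 1.3550)/0.6832] = Φ(0.871) = 80.8%. The inflation also reproduces: 169/(0.80 × 0.95) = 222.4, so 223.

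**2. Power of the named test.** All pairs of outcomes from Binomial(n, 0.47) and Binomial(n, 0.32) were enumerated. The probability of every pair with a two-sided p-value of at most 0.05 was summed.

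| Evaluable per group | Fisher exact | Uncorrected chi-square |
|---|---|---|
| 169 | 78.0% | 81.2% |
| 179 | 79.9% | 82.9% |
| 180 | 80.2% | 83.0% |

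Fisher's test first reaches 80% at 180 per group. With the same inflation, 180/0.76 = 236.8, so 237 per group, which is 14 more than planned. The continuity-corrected formula, which approximates Fisher's test, gives 179.

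The loss comes from conservatism. With both rates at 39.5% and 169 per group, the true type I error is 4.0% for Fisher's test and 5.2% for the uncorrected chi-square, so a small part of the chi-square's advantage is a size slightly above nominal.

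**3. A test stratified by centre.** A Cochran-Mantel-Haenszel test was simulated one million times, with 85 and 84 evaluable patients per arm in the two centres and 47% versus 32% in each. Power was 81.2% without continuity correction and 78.1% with it. The correction removes the gain, so the plan must say which is used.

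**4. The other two inputs.**

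- Same 15-point difference from 65% (65% to 50%): 169.3, so 170 per group by the pooled formula. Fisher power at 169 is 77.7%.
- Relative 15% reduction (47% to 39.95%): 775 per group. Power at 169 is about 26% (normal approximation) or 23% (Fisher). The stated 169 therefore fits only percentage points.

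**The case against.** The strongest reply is that nothing in the Sample size section is miscalculated. Both 169 and 223 follow from the stated inputs, planning by normal approximation and analysing with Fisher's test is common, and the section does not say that the 80% was computed for Fisher's test. Two points of power is also less than the uncertainty in a base rate given only as approximate. All of this stands, and it limits the point: 169 is not wrong, and the trial need not be enlarged. It does not make 80% the power of the chosen primary test.

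A reader might infer more from the same passages, and the documents do not support it:

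- **That the sample-size statement fails as a whole.** It does not; step 1 reproduces it.
- **That 169 was computed from a base rate other than 47%, because 65% versus 50% gives 169.3.** A required size is rounded up, so 169.3 gives 170. Other inputs also come close: 49% versus 34% gives 168.2, which rounds up to 169. Nothing identifies such a source.
- **That 47% and 65% contradict each other.** The article refers to more than one pilot: an earlier one on symptoms persisting at 3 months (Background), and SOFTER Pilots 1 and 2 (Study enrollment procedures and randomization). The 47% may come from the earlier pilot, and the article does not say that the randomized pilot used the same score cut-off. What remains is an unnamed source, with almost no effect on the sample size (170 instead of 166).
- **That the trial was planned for a relative 15% reduction it cannot detect.** The stated sample size rules this reading out.

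**Conclusion.** The point holds in a limited form. With a two-sided 5% level and 47% versus 32%, the primary Fisher test has 78.0% power at 169 evaluable patients per group, and 80% needs 180. The stated 80% holds for an uncorrected chi-square-type test (81.2%). The discrepancy is about 2 percentage points. It concerns agreement between the stated power and the named test, not the number to enrol.

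The base rate and the effect wording are minor clarifications. The 18-point gap between 47% and 65% is unexplained rather than proven inconsistent. The effect wording is ambiguous, but the stated sample size resolves it for a reader who does the calculation.

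**What to change.** Choose one of the following; neither adds patients.

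1. In Data analyses, make the primary test a Cochran-Mantel-Haenszel test stratified by centre, without continuity correction. Centre is already the randomization factor, so the test also matches the design. Power at 169 is about 81%. The cost is a documented change of primary test, made before allocation is revealed to the analysts.
2. Keep Fisher's test and restate the power in Sample size as 78% at 169 evaluable patients per group. The cost is one sentence and a slightly less favourable figure.

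In either case, state that the 5% is two-sided, if that was intended.

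Minor clarifications, wording only:

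- In the Abstract (Methods) and Sample size, write the effect as 15 percentage points (47% to 32%).
- In Sample size, name the pilot, arm and score cut-off that gave 47%, and explain how it relates to the 65% under usual care in the Background. The cut-off itself must be reconciled first: Inclusion criteria require a score above 1, while Study enrollment procedures and randomization require one above a threshold of 2.
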